## Abstract

**Introduction:** One of the major problems with inpatient treatment of adolescent girls with an eating disorder (ED) is that the strategies learned during their hospital stay are not easily applied or maintained in their daily lives, and this has been related to high rates of relapse and readmission. The ECHOMANTRA programme was developed to optimize outcomes during and following inpatient or day-patient treatment. ECHOMANTRA is based on interventions for carers (Experienced Carers Helping Others, ECHO) and patients (Maudsley Model of Anorexia Nervosa Treatment for Adults, MANTRA) and is developed from the cognitive interpersonal model of anorexia (Schmidt and Treasure, 2006; Treasure and Schmidt, 2013). This study aims to describe the study protocol of a randomized controlled trial (RCT) for evaluating the efficacy of an adaptation of a novel intervention for patients and carers (ECHOMANTRA) to be implemented as an add-on to treatment-as-usual (TAU).

**Method:** In a multi−center pilot RCT, 80 female adolescent patients with a DSM-5 diagnosis of an ED and their carers will be invited to participate in the study. They will then be randomized to receive either the ECHOMANTRA intervention as an add-on to TAU or TAU alone. A repeated measures design will be conducted across four time points. Primary outcomes will be patient psychological well-being and eating disorder symptoms, and secondary outcomes will include body mass index, obsessive-compulsive symptoms, perfectionism, motivation to change and psychosocial adjustment. For carers, outcome variables will include psychological well-being, expressed emotion, accommodation and enabling behaviors, burden, and care skills.

**Discussion:** The results from this trial will establish the effectiveness of ECHOMANTRA and may reveal whether and to what extent this novel intervention can optimize outcomes during and following inpatient treatment. This study will also provide the adaptation of the ECHOMANTRA in the Spanish context for inpatient/day-care treatment.

## Introduction

Eating disorders (ED) are extremely complex multi-causal mental health illnesses, which have serious medical complications and especially affect adolescents and young women (López and Treasure, 2011). The most frequent diagnosis in adolescents is Other Specified Feeding and Eating Disorder (OSFED) followed by Anorexia Nervosa (AN) and finally Bulimia Nervosa (BN) (Swanson et al., 2011). These disorders are characterized by serious symptoms as well as a high degree of comorbidity and mortality (Nordbo et al., 2012; Saldaña et al., 2014; Fichter and Quadflieg, 2016); consequently, patients need to be hospitalized on many occasions. One of the major problems with hospital treatment is that although these patients learn strategies during their hospital stay, they have difficulty in being able to apply and maintain them in their daily lives. As a result, there is a high rate of relapses and readmissions, which have been related to resistance to treatment, low motivation to change, severe pretreatment caloric restriction, low body mass index and higher occupational and social stress (Fairburn, 2008; Kaplan et al., 2009; Grilo et al., 2012; Hoang et al., 2014; Morris et al., 2015; Vall and Wade, 2015). A recent meta-analysis study found that the risk of relapse is especially high during the first year after the end of treatment (Berends et al., 2018; Khalsa et al., 2017). High relapse rates reveal the need to optimize patient treatments after hospital admissions by supporting inpatient/day care and community transition through promising targeted psychological interventions (Bryan et al., 2021).

In response to this, [name] team developed the ECHOMANTRA intervention programme, as a means of facilitating the transition from inpatient hospital treatment to daily life and to the community (Treasure and Schmidt, 2013; Treasure et al., 2015; Cardi et al., 2017). This programme is based on scientific evidence that demonstrates that interventions directed at these patients as well as their carers improve the outcomes in these patients’ health. Involving the family in the treatment of ED is a key strategy in their recovery and it also strengthens patients’ social networks and eliminates their isolation and loneliness, which contribute to maintaining the disorder (Levine, 2012; Treasure and Nazar, 2016; Sepúlveda et al., 2020). A study was recently published with the preliminary results of ECHOMANTRA intervention with AN inpatients and their carers in the United Kingdom (Adamson et al., 2019). A case series study was employed using a mixed-methods approach to measure the feasibility and efficacy of augmenting intensive hospital treatment with ECHOMANTRA. Results showed that patients’ symptomatology improved after the ECHOMANTRA intervention and was maintained in the follow-up. In addition, there was a reduction in carer burden and an improvement in skills, so it was concluded that the efficiency of hospital attention for ED can be increased by preparing both patients and their carers for the transition after hospitalization.

ECHOMANTRA consists of an intervention programme for ED carers (ECHO; Experienced Carers Helping Others; Treasure et al., 2015) and another programme for patients (MANTRA, Schmidt et al., 2014). MANTRA is recommended for the treatment of adults outpatients with AN (National Institute for Health and Care Excellence [NICE], 2017). It is based on the Cognitive Interpersonal Maintenance model of AN (Schmidt et al., 2014), which was developed as a proposed theoretical framework that would synthesize the most important internal and interpersonal maintaining factors of this disorder. MANTRA intervenes in the emotional regulation and eating behavior of these patients, putting a special emphasis on behavior change strategies. This programme focuses on the steps that will help patients thrive in their transition from inpatient care to daily life as well as generating cognitive and behavior changes and strengthening relationships with their family and social groups. It is a flexible treatment programme which directly involves patients in the therapeutic process. To date, it has not been applied to adolescents with an ED; however, some of its characteristics might be especially beneficial to them. In fact, it has been published the study protocol of a recent research that analyses the feasibility, acceptability and efficacy of the MANTRA treatment programme for adolescents patients (Wittek et al., 2021). MANTRA includes content that is prevalent and important to address across the spectrum of ED and in adolescent patients.

The ECHO part of the intervention focuses on carers. Based on the Model of Carer Coping (Treasure et al., 2003), this part of the programme reveals the different aspects that influence coping which can be problematic for carers as they represent sources of psychological distress. The programme provides assistance, support and training for carers to enable them to cope with their role. It teaches them how to reduce and manage their expressed emotion and symptom accommodation, and to deal with difficult and problematic situations that arise. In addition, ECHO teaches skills for positive communication and behavior change so carers will be able to support their loved ones in their recovery. Different studies using the ECHO have shown that the intervention in both the adult and adolescent groups led to a moderate reduction in time spent caring and also in bed use. Moreover, through this programme there was a small to moderate improvement in the wellbeing of both carers and patients in the intervention group (Hibbs et al., 2015a; Magill et al., 2016; Hodsoll et al., 2017). Our research group applied an intervention programme based on the ECHO to carers of ED patients in Spain. The results obtained showed that carers who participated in the programme improved their levels of well-being, reducing carer burden, psychological distress, and expressed emotion. In addition, only patients whose carers participated in the programme reduced their levels of anxiety, depression, and psychological distress while no change occurred in patients whose carers participated in the control group (Pérez-Pareja et al., 2014; Quiles Marcos et al., 2018). A recent review study analyzing the effectiveness of treatments for carers of ED patients concluded that ECHO also provides an intervention that can reduce service costs (Treasure et al., 2021).

The aim of this paper is to describe the study protocol of a randomized control trial (RCT) aimed at evaluating the efficacy of a novel intervention for patients and carers, called ECHOMANTRA, adapted to be used as an add-on to treatment-as-usual (TAU; inpatient treatment or intensive day-care treatment) compared to TAU alone.

### Hypotheses

•Patients from the experimental group (TAU + ECHOMANTRA) will show significantly greater improvements in health outcomes (body mass index, ED symptoms, psychological well-being, psychosocial adjustment, perfectionism, obsessive-compulsive symptoms, motivation to change), and other efficacy indicators as readmission, in comparison to patients from the control group.•The efficacy of the combined intervention (TAU + ECHOMANTRA) will be stable in the short (6 months) and middle term (9 months).•Carers from the experimental group will present a better psychological well-being and lower illness accommodation, expressed emotion and burden in comparison to carers from the control group.•Carers from the experimental group will have more ED carer skills in comparison to carers from the control group.

## Methods and Analyses

This study has been registered on the ISRCTN registry (Trial Identifier: ISRCTN43554732). CONSORT 2010 for parallel group randomized trials (Schulz et al., 2010) is specifically observed in reporting this trial.

### Study Design and Procedure

This is a multi-center, pilot, randomized, controlled, blind, superiority study with two parallels groups. Assignment to the control or experimental group will carry out using a computer-generated randomized sequence, with1:1 treatment allocation. The research assistant at each center will conduct a semi-structured interview to evaluate participants and confirm fulfillment of the inclusion/exclusion criteria. Patients who are receiving ED treatment (either as inpatients or day-patients) and fulfill the inclusion criteria, will be invited to participate in the study together with a carer. By “carer” we refer to someone who usually takes care of the patient outside the hospital/day-center and lives with her. Patients and carers will receive detailed information on the study and will be asked for a written informed consent to be able to participate. After submitting the consent form, participants will be invited to complete the baseline questionnaires and will then be randomly assigned to either (1) ECHOMANTRA in addition to TAU or (2) TAU only (see Figure 1). The ECHOMANTRA-guided skills-sharing intervention will include materials and eight online sessions (one per week) for carers and patients, while treatment duration will be 8 weeks.

**FIGURE 1 F1:**
[figure not shown]
Study design flow diagram.

### Participants

#### Patients

Patients will be recruited from three different specialist inpatient/day-patient eating disorder units (Eating Disorders Inpatient Unit at the San Juan Hospital; CREA, Centre for emotional and nutritional recovery, Eating Disorders Day Centre; ADANER, Association for the defense of AN and BN care, Eating Disorders Day Centre). This study will involve adolescent girls who have received an eating disorder diagnosis according to the fifth edition of the Diagnostic and Statistical Manual of Mental Disorders (DSM-5) criteria (American Psychiatric Association, 2013), including diagnoses of AN, BN, and OSFED. The inclusion criteria will be as follows: (1) aged between 12 and 19, (2) no psychiatric comorbidity, (3) receiving treatment for ED in a specialist inpatient/day-patient ED unit, (4) a family member willing to participate in the study and (5) ability to manage an electronic device (e.g., mobile phone, computer, laptop or tablet) and the Internet in order to access the online sessions, (6) a native Spanish speaker or understands native level Spanish. Patients will be asked to nominate a carer to whom the researcher will invite to participate in the trial. One carer per patient will be permitted, and this should be a primary carer, somebody who usually takes care of the patient outside the hospital/day-center and lives with her.

#### Carers

For carers/family members the inclusion criteria will be as follows: (1) living with the patient and (2) not suffering from a serious medical or psychiatric condition (this information will be assessed through a self-report) and (3) ability to access an electronic device (e.g., mobile phone, computer, laptop or tablet) and the Internet in order to access the online sessions and (4) a native Spanish speaker or understands native level Spanish.

### Randomization

After screening and consent, patients and their carers will be randomized as a dyad using a randomized computer-generated sequence. A full randomization procedure macro will be applied saving the “seed” (SEED = 13012021) to reproduce the exact selection. Randomization will be facilitated by [name], a colleague from the Behavioral Sciences and Health Department, who will be not involved in this study. Once the allocation has been assigned, no changes can be made. Those randomized to the intervention arm (ECHOMANTRA plus TAU) will have access to the intervention materials.

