### Interventions/Treatment Arms

#### Treatment as Usual

We have chosen not to use a standardized comparison treatment as this would require practical changes in different settings and resource management (including training, supervision and quality control), which will not be feasible. We have therefore chosen to allow centers to follow their own procedures for TAU. We will stratify our analyses by center, which will be adjusted accordingly for any bias.

For TAU inpatient care, the Eating Disorder Unit at the San Juan Hospital will provide a programme using a multidisciplinary team approach (dietician, psychologist, physician and nurse). It will include monitoring of physical risks, nutritional rehabilitation, education on healthy eating and nutrition patterns. Besides it will try to modify/improve thoughts, attitudes, behaviors and feelings that maintain the illness through psychological therapy. Once a patient has stabilized and reached a healthy body mass index, she is discharged. She is then either followed up to assess her progress and to facilitate transition to home or she is referred to a day care center.

Treatment-as-usual in the day care centers (ADANER and CREA) will involve multidisciplinary treatment including dietetic support, psychological interventions, school education, and when appropriate, sessions with psychiatrists. Patients will receive the following psychological interventions: weekly individual cognitive behavioral therapy for eating disorders (CBT-ED); and psychoeducational group therapy on nutrition, emotion management, body image, social skills and problem-solving strategies. Usually, patients attend every day of the week (from Monday to Friday) for an average of 6 h. They receive psychological intervention sessions and they also make the different meals of the day. Parents/carers can also access a fortnightly parent support group.

The TAU-only (control condition) group will have no access to the intervention materials or the ECHOMANTRA intervention sessions. At the end of the study, individuals randomized to the TAU-only condition will be offered the self-help components of the intervention.

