### Statistical Analysis

Firstly, a covariance analysis (ANCOVA) will be carried out using the pre-test scores as a covariate to analyze the impact of the combined intervention. Secondly, a repeated measures analysis of variance will be used to analyze the short and medium-term efficacy of the combined intervention in comparison to the usual intervention between and within groups at different time points, and effect size values will also be considered. Stratification will be performed in the analyses by the admission center and “diagnosis” variable will be controlled. IBM SPSS Statistics 24.0 will be used for all the analyses (IBM Corp, 2016).

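### The protocol article publishes the working randomisation seed while recruitment is still described as to come, which needlessly weakens concealment; adding centre to the allocation would be a modest further gain

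*Protocol article*

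**What the plan says.** All references are to the protocol article.

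- **Randomization.** The dyad is the unit: "patients and their carers will be randomized as a dyad using a randomized computer-generated sequence". On the method: "A full randomization procedure macro will be applied". The seed is saved, and its value is printed together with its purpose: "SEED = 13012021) to reproduce the exact selection". The work is done by a colleague "who will be not involved in this study". The macro's name, its settings and the length of the list are not given.
- **Study Design and Procedure.** The sequence is a "computer-generated randomized sequence, with1:1 treatment allocation". A research assistant at each centre confirms eligibility. Consent and baseline questionnaires come before assignment. Invitation, consent and assignment are all in the future tense.
- **Blinding.** Participants and therapists know the condition. The sequence creator is outside the research team and has no other role.
- **Centre.** Participants lists three units, one inpatient and two day centres. Under Treatment as Usual each centre follows its own procedures, and the remedy offered is in the analysis: "We will stratify our analyses by center, which will be adjusted accordingly for any bias". Statistical Analysis repeats it: "Stratification will be performed in the analyses by the admission center". Neither section that describes allocation mentions centre, strata or blocks.
- **Size.** The Abstract gives 80 patients. Sample Size ends with at least 70 per group, which is 140.

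**The concern.** A seed is archived so that a list can be audited afterwards, and nothing is gained by making it public before the last dyad is allocated. Here it appears in a text that presents enrolment as lying ahead, so one of the items needed to rebuild the list is open to anyone, including staff who screen and invite patients. Therapists are unblinded and eligibility is judged locally. Someone able to foresee the next assignment could therefore influence who is invited and when, and no adjustment in the analysis repairs selection bias of that kind.

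A lesser matter concerns the same list. The article treats centre as important enough to stratify the analyses, because usual treatment differs between centres, yet it describes allocation as a single sequence without a centre factor. Uneven arms within a centre cost some precision. They also thin the comparison by therapeutic context that the Discussion hopes to make.

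**Working it through.** **1. What is needed to rebuild the list.** This part is reasoning, not arithmetic.

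| Item | In the article? |
|---|---|
| Seed | Yes, 13012021 |
| Macro and version | No, described only as a full randomisation macro |
| Settings and arm coding | No |
| List length | Not fixed: 80 (Abstract) or at least 2 × 70 = 140 (Sample Size) |

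One item is public. A reader of the article alone cannot rebuild the list; a person who also has the others can, by the article's own statement of what the seed does.

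**2. Chance of an uneven centre under one unstratified sequence.** The article gives no centre sizes, so these are assumptions: 27/27/26 for 80 dyads and 47/47/46 for 140, with a less equal pattern as a check. Arms were allocated either by independent fair draws (simple) or by permuting a list with equal arm totals (fixed). The event is that at least one of the three centres splits 65:35 or worse; for a centre of 27 that means 18:9 or worse. Results are from simulation.

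| Centre sizes | Fixed totals | Simple |
|---|---|---|
| 27/27/26 | 16% | 36% |
| 40/20/20 | 34% | 50% |
| 47/47/46 | 4% | 13% |
| 70/35/35 | 9% | 18% |

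Under simple randomisation of 80, the arm totals differ by 10 or more with probability 31% (binomial, 80 draws at 0.5). A 45:35 total still keeps 4 × 45 × 35 / 80² = 98.4% of the information.

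**3. What that imbalance costs once centre is in the model.** With *a* of the *m* dyads of a centre in one arm and a common residual variance, the centre contributes information proportional to a(m − a)/m, which is at most m/4. The loss is 1 − Σ[a(m − a)/m] ÷ (N/4). Taking expectations over three centres:

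- Simple: 3/N. At 80: 3/80 = 3.75%. At 140: 3/140 = 2.1%.
- Fixed totals: (3 − 1)/(N − 1). At 80: 2/79 = 2.5%. At 140: 2/139 = 1.4%.

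Neither expression depends on how the dyads are spread over the centres. Simulation agrees: 2.5% to 3.7% at 80, with a 95th percentile of 7.5% to 9.6%, and 1.4% to 2.1% at 140. In dyads, the mean loss is about 2 to 3 (2.5% × 80 = 2; 3.75% × 80 = 3). A centre split 65:35 keeps 4 × 0.65 × 0.35 = 91% of its information.

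**4. With stratified blocks.** Taking block size 4 as an illustration, the arms in a centre differ by at most 2. The worst split in a centre of 26 is 14:12, which keeps 4 × 14 × 12 / 26² = 99.4%. A 65:35 split cannot occur at these sizes.

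**The case against.** The case for leaving the plan alone has real weight. A seed by itself does not give the list, and stating that it reproduces the selection describes an audit facility for whoever holds the macro. Someone with no other role makes the sequence, allocation follows screening, consent and baseline, and assignments cannot be changed afterwards. The future tense is the usual style of a protocol article, so it does not prove that recruitment was open when the text became public. All of this stands. A reader might infer from the printed seed that every coming allocation is predictable, or that concealment has failed; the documents support neither, because the other items are not printed and nothing shows that recruiting staff held them.

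On centre, the absence of stratified allocation is inferred from the description and is not stated, and a condensed article may leave strata and blocks to the full protocol. Unstratified allocation is also a valid, unbiased choice when centre is handled in the analysis. A reader might take a 36% chance of a 65:35 centre as a serious threat to the result; after centre adjustment it is not, as the small information loss shows. Blocking in unblinded centres also brings some predictability of its own.

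What remains is that publishing the working seed ahead of recruitment brings no benefit, weakens the main concealment safeguard described, and costs almost nothing to put right.

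**Conclusion.** The point holds as a conditional weakness of concealment. The article discloses one item needed to regenerate the list, in a trial with unblinded therapists and local eligibility decisions, and describes enrolment as still to come. How likely misuse is cannot be put as a figure, because it depends on who holds the macro, its settings and the list length, and on whether dyads remained to be randomised. None of this is in the documents.

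Stratifying allocation by centre is secondary. The mean loss it would avoid is about 1% to 4% of the information, or 2 to 3 dyads. This assumes a single 1:1 sequence without centre as a factor, a common variance, complete data, and one pooled model with centre as a covariate. If the stratified analyses were meant as separate analyses per centre, the split within a centre would matter more. The probabilities of an uneven centre rest on assumed centre sizes; the mean loss does not.

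**What to change.** - **If dyads remain to be randomised:** the same independent colleague generates a new list for them from an undisclosed seed. Seed, macro and settings are filed until recruitment closes, and the working seed is removed from public text.
- **If enrolment is complete:** report who had access to the seed and macro during recruitment, and give the allocation by centre.
- **Secondary:** generate the new list stratified by centre with randomly varying, undisclosed block sizes, or state that allocation is unstratified and why. Keep centre as a covariate in one pooled model.
- **List length:** reconcile 80 with at least 140, since the planned number also fixes the length of the list.

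The order of baseline before assignment in Study Design and Procedure is already sound and needs no change. The cost is about an hour of the colleague's time and a short amendment. Blocking adds slight predictability, which random block sizes limit.
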